### Control group

The control group will have "usual" care that is provided by the rehabilitation staff. However, neither treating staff nor patients in the control will receive data on walking times to aid the setting of walking time targets.

### Data Collection

- Walking times will be collected using the accelerometer. The accelerometer will also provide daily sitting, standing and lying times. At night, when the accelerometer is not being worn, it is assumed that the patient is lying down; lying times will be imputed accordingly.
- Lower extremity function will be assessed by the RA at entry into the project, on the 14th day and at discharge or exit from the project, using the Short Physical Performance Battery.
- Change in mobility status (whether walking independently or requiring supervision) will be assessed and recorded weekly by the AM.

- The interRAI AC PAC instrument will be administered by the RA within 3 days of entry into the project, at the 14th day and at discharge or exit from the project.
- The Short Self-Efficacy and Outcome Expectation for Exercise Scales will be administered by the RA at entry and exit from the project.
- Health-related quality of life will be measured using the EQ-5D administered by the RA at study entry and exit, as well as at the 28 day post discharge follow-up.
- A telephone follow-up by the RA at 28 days post exit from the study will assess functional status [Activities of Daily Living (ADLs) and locomotion from the interRAI AC PAC, quality of life (EQ-5D) and adverse outcomes such as readmissions to hospital or changes to a higher level of care (e.g. community to residential aged care)].

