### Outcomes

The primary outcome measure will be walking time per day collected using the accelerometer. The accelerometer devices used in this study are tri-axial ALIVE Heart and Activity Monitors, manufactured by Alive Technologies Pty. Ltd. The device is 90mm X 40mm X 16mm, weighs 55g with the battery, and measures acceleration in 3 directions using a spring mass system. A single device is fitted in a pouch attached to a belt worn around the waist.

Secondary outcome measures will include lower extremity function and functional status, quality of life (QoL), length of stay, post discharge hospital readmissions or differences in level of care.

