### Feasibility of recruiting required sample size

Based on a conservative recruitment rate of 2 patients per week at each site, it would take 48 weeks to complete data collection for 90 patients (270 for the 3 sites) based on an average length of stay of 4 weeks. A minimum of 8 accelerometers would be required per site.

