### Study procedure

For both groups the AM will show the study participants how to put on the accelerometer belt which they are required to wear from rising to going to bed (and for at least 8 hours) each day over the study period. The participant will remove the accelerometer belt in the evening and when showering. The AM will monitor and record the level of compliance with wearing the accelerometer. In addition the AM will obtain from the treating physiotherapist the daily time spent in therapy sessions.

For each participant, the duration of the study is expected to be 28 days (4 weeks) unless in the interim, the patient is discharged or unable to continue in the study by virtue of a sudden change in condition which precludes mobility. Each weekday morning, the AM will download data from the accelerometers for daily readings of walking time, (and other activity measures).

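### The final follow-up has two anchors, 28 days after discharge and 28 days after study exit, and the exit anchor shortens the readmission window for patients still in hospital at exit

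*Protocol*

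**What the plan says.** Two consecutive bullets in the protocol's Data Collection section time the same contact differently.

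- The quality-of-life bullet places EQ-5D at study entry and exit, "as well as at the 28 day post discharge follow-up".
- The telephone bullet reads "A telephone follow-up by the RA at 28 days post exit from the study will assess functional status", and goes on to list EQ-5D, readmissions and moves to a higher level of care.

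Exit and discharge are not the same event. Study procedure says that "the duration of the study is expected to be 28 days (4 weeks) unless in the interim, the patient is discharged or unable to continue" because of a change of condition that rules out walking. Exit is therefore the earliest of discharge, day 28 and such a change. Data Collection also treats the two as distinct when it schedules assessments "on the 14th day and at discharge or exit from the project".

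Outcomes lists "length of stay, post discharge hospital readmissions or differences in level of care" as secondary measures, so readmission is counted from discharge and length of stay is itself an outcome. The feasibility paragraph plans "based on an average length of stay of 4 weeks". The Economic Analysis section costs readmissions over the follow-up period without giving that period a start or an end.

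**The concern.** For a patient discharged by day 28 who did not leave the study early, the two bullets give the same date. For anyone who exits before discharge they do not, and nothing in the protocol says which governs.

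A call timed from exit then falls partly or wholly within the index stay. A patient who has not been discharged cannot be readmitted and has no settled level of care to report. The call is the only described source of readmission data after exit, so days it does not cover cannot be recovered at analysis. Sites could also follow different bullets.

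A second, milder issue is that both anchors move with length of stay. The last EQ-5D is therefore taken at different times from randomisation in different patients. This matters for the planned within-trial cost-utility analysis if stay differs by arm.

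**Working it through.** The protocol states no figure on this point, so there is none to reproduce. The sample size rests on walking-time inputs only, and follow-up timing does not enter it.

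**1. Dates under each anchor.** Let D be the day of discharge counted from study entry, with no early exit for change of condition.

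- Exit = min(D, 28).
- Call under the exit anchor = min(D, 28) + 28.
- Call under the discharge anchor = D + 28.
- Days at risk of readmission = call day − D, not below 0.

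| D | Call, exit anchor | Call, discharge anchor | Days at risk, exit anchor | Days at risk, discharge anchor |
|---|---|---|---|---|
| 14 | 42 | 42 | 28 | 28 |
| 21 | 49 | 49 | 28 | 28 |
| 28 | 56 | 56 | 28 | 28 |
| 35 | 56 | 63 | 21 | 28 |
| 42 | 56 | 70 | 14 | 28 |
| 56 | 56 | 84 | 0 | 28 |

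The anchors part only when D exceeds 28. Early exit for change of condition can part them sooner. As an illustration, exit on day 10 with discharge on day 40 puts the exit-anchored call on day 38, before discharge.

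For discharge on day 14 or later, without early exit, the last EQ-5D falls on days 42 to 56 from entry under the exit anchor. Under the discharge anchor it falls on day D + 28, with no upper limit.

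**2. How many patients are affected.** The protocol gives a mean stay of 4 weeks and no SD. Assume a lognormal time from entry to discharge with a coefficient of variation (CV) of 0.3 to 0.7.

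| Mean from entry (days) | Still in hospital at day 28 | Their mean days at risk, exit anchor |
|---|---|---|
| 21 | 13% to 22% | 16 to 23 |
| 28 | 38% to 44% | 14 to 21 |
| 35 | 52% to 73% | 12 to 17 |

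Early exits for change of condition are not counted here.

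**3. Effect on one patient.** Assume a constant hazard giving 15% readmission over 28 days (not a protocol figure). Recorded risk over k days at risk = 1 − 0.85^(k/28).

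- k = 21: 11.5%
- k = 14: 7.8%
- k = 7: 4.0%
- k = 0: 0%

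**4. Effect on the comparison of arms.** Use the same hazard, with mean stay 28 days in one arm and 24 in the other, CV 0.3 to 0.7 and no true effect on readmission.

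- Exit anchor: spurious difference of about 0.8 to 0.9 percentage points (at CV 0.5, 12.6% against 13.5%), with more readmissions recorded in the shorter-stay arm.
- Discharge anchor: zero, because every patient has 28 days at risk.
- Fixed call at day 56 from randomisation: about 1.6 to 2.0 points. Days at risk become 56 − D, that is 42, 14 and 0 for discharge on days 14, 42 and 56, with recorded risks of 21.6%, 7.8% and 0%.

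**The case against.** The strongest defence is that this is a slip of wording in a secondary follow-up. Most sites would read exit as discharge, and the two coincide for every patient discharged by day 28 without early exit. The 4-week stay is a planning figure for recruitment and devices (2 patients a week × 4 weeks = the 8 accelerometers per site). It has no spread and is not said to run from entry. Some patients enter only once ready to mobilise and when a device is free, so if the 4 weeks run from admission, fewer remain in hospital 28 days after entry. This stands as a limit on size: the affected share is uncertain, hence the wide range. It does not remove the conflict, because the protocol itself separates exit from discharge.

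A reader might go further and infer that readmission is compared over unequal windows whichever anchor is used. The document does not support that: the discharge anchor gives everyone 28 days and matches the outcome as named. Nor does it show a biased comparison between arms. The 11.5%, 7.8% and 4.0% describe individual late-discharge patients, and nothing in the protocol shows that stay will differ by arm.

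A reader might also infer that one fixed call at day 56 from randomisation cures everything. It would equalise EQ-5D timing, but for post-discharge readmission it roughly doubles the artefact of the exit anchor.

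**Conclusion.** The protocol gives one follow-up contact two anchors, and they disagree for every patient whose exit precedes discharge. Under the exit anchor these patients have fewer than 28 days, possibly none, at risk of the readmission outcome the protocol names. The share still in hospital at day 28 is about 13% to 73% under assumed lognormal stays with a mean of 21 to 35 days from entry. The resulting bias between arms is small unless stay differs: about 1 percentage point for a 4-day difference, assuming 15% readmission per 28 days and a mean stay of 28 days in the longer-stay arm.

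The variation in EQ-5D timing from randomisation holds under either anchor. Whether it differs between arms is open. The primary outcome, primary analysis and sample size are untouched, so this should be fixed but does not threaten the main result.

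**What to change.** Reconcile the two Data Collection bullets so that one anchor governs, and time the call that records readmission and level of care at 28 days after discharge, to match the Outcomes section. State that this also applies to patients who exit at day 28 or earlier while still in hospital.

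If EQ-5D and QALYs, total hospital days and costs are to be compared over a common horizon, define that horizon from randomisation as a separate, optional choice. Do not apply it to post-discharge readmission.

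The anchor change costs a line of protocol text and an eCRF scheduling rule, with the same single call. Sites must track the discharge date after study exit, which the length-of-stay outcome already requires. The downside is that patients with long stays are called later (day 70 rather than day 56 for discharge on day 42), so their EQ-5D lies further from randomisation. The optional horizon could need an extra EQ-5D contact for patients whose post-discharge call falls on another day.

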## Analysis

The primary analysis will be based on the repeated daily measures of walking time, compared between the intervention and control groups. Appropriate repeated measure technique will be adopted to analyse this data, depending upon the nature of the distribution of walking time. The changes in the scores related to lower extremity function, EQ-5D and other data between baseline and follow-up will be analysed using appropriate non-parametric techniques. InterRAI generated information will be compared between the groups using appropriate statistical techniques. All analyses will be based on 'Intention to Treat' population.

A formal statistical analysis plan will be in place once the study protocol is finalised and approved. No interim analysis is planned for this study. The data management, statistical analysis and the reporting of the study will strictly follow the standard operation procedures adopted by the Queensland Clinical Trials & Biostatistics Centre.

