## Economic Analysis

A "with-in trial" economic analysis will be undertaken from the perspective of the healthcare system. The research costs will be excluded from this analysis so that the intervention group (with daily feedback on walking times) can be compared to a usual care group (who receive general discussion around mobility goals). This enables results to be generalised beyond a research setting.

We will collect data to accurately record costs at the patient and ward levels. Cost data will include staff and technician time in applying the accelerometer, downloading and analysing data, and AM time to feedback the previous day's walking achievements to the patient. Ward costs include a national average per diem cost for length of stay and any costs for readmissions during the follow-up period. Equipment costs will include accelerometers, computation and printing. The outcome data (including walking time, length of stay and quality of life) will enable both cost-effectiveness and cost-utility analyses to be performed. Sensitivity analyses will enable these estimates to be adjusted for expected cost reductions associated with increased use (more patients per ward will secure economies of scale) and price reduction as the technology improves.

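### SPPB, EQ-5D and other scale scores are committed to non-parametric analysis of change from baseline, which is less precise than a baseline-adjusted comparison

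*Protocol*

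**What the plan says.** The Analysis section of the protocol treats three groups of outcomes differently.

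- **Daily walking time (primary):** a repeated-measures method, to be chosen according to how walking time is distributed.
- **Scale scores:** the object of analysis is "The changes in the scores related to lower extremity function" and similar measures, and the method is stated without any such condition: "lower extremity function, EQ-5D and other data between baseline and follow-up will be analysed using appropriate non-parametric techniques".
- **InterRAI outcomes:** "InterRAI generated information will be compared between the groups using appropriate statistical techniques". No class of method is fixed.

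The same section adds: "A formal statistical analysis plan will be in place once the study protocol is finalised and approved".

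The Data Collection section shows that the baselines exist. For the SPPB: "Lower extremity function will be assessed by the RA at entry into the project, on the 14th day and at discharge" or exit. For the EQ-5D: "Health-related quality of life will be measured using the EQ-5D administered by the RA at study entry and exit", and again at the follow-up 28 days later. The exercise self-efficacy and outcome-expectation scales are given at entry and exit. I take these to be part of the otherwise undefined remaining data in the Analysis sentence.

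**The concern.** Most detail on secondary analyses can properly wait for a SAP. This sentence does not wait. It settles that the scores are analysed as changes and that the method is non-parametric, and a SAP faithful to the protocol inherits both choices. The protocol makes the primary method depend on the distribution but does not extend that to the scale scores.

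The choice of change score matters more than the choice of a rank method. Subtracting the baseline in full is right only if the regression slope of follow-up on baseline is 1. When the slope is smaller, subtraction adds baseline noise to the comparison. When the correlation is low enough, it does worse than ignoring baseline altogether. At stake is the precision of the comparisons of function and quality of life, which serve the protocol's secondary aim on patient outcomes. The primary result is not at stake.

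**Working it through.** **1. The protocol's own sample size.** Inputs from the Sample size and power analysis section: SD 51 minutes, difference 15 minutes, baseline-to-follow-up correlation 0.20, correlation among follow-ups 0.60, 80% power, 5% significance (taken as two-sided).

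n per group = 2 × (51 × (1.960 + 0.842)/15)² × f = 181.47 × f

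With k follow-up days, the mean of the follow-ups has relative variance p = (1 + (k − 1) × 0.60)/k. This is 8.8/14 = 0.6286 for 14 days and 12.4/20 = 0.6200 for 20 days.

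| Analysis | f | 14 days (stated 108) | 20 days (stated 105) |
|---|---|---|---|
| Follow-up only | p | 115 | 113 |
| Change from baseline | p + 1 − 2 × 0.20 | 223 | 222 |
| Baseline-adjusted | p − 0.20² | 107 | 106 |

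Only the baseline-adjusted form comes within one patient of both stated figures. Then 108/0.8 = 135 per group, or 270 in total, as stated. The calculation for walking time is therefore consistent with baseline adjustment. The change-score form would need about twice as many patients.

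**2. Change score against adjustment for one follow-up.** Let σ₀ and σ₁ be the baseline and follow-up SDs.

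- Change score: variance σ₀² + σ₁² − 2rσ₀σ₁
- Baseline-adjusted: variance σ₁²(1 − r²)
- Difference: (σ₀ − rσ₁)², which is never negative

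So for mean-based analyses in large samples the change score is never more precise, whatever the two SDs. With σ₀ = σ₁ the ratio of adjusted to change-score variance is (1 − r²)/(2(1 − r)) = (1 + r)/2. The change score is also less precise than follow-up alone when 2(1 − r) > 1, that is, when r < 0.5.

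**3. Size.** The protocol gives no r for SPPB, EQ-5D or the exercise scales. Its 0.20 is for daily walking time and should not be carried over. The r values below are assumptions. The power columns take the effect at which a baseline-adjusted mean comparison has 80% power:

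- mean change: Φ(2.802 × √((1+r)/2) − 1.960)
- rank test of change: the same, with (1+r)/2 multiplied by 3/π, the efficiency of the Wilcoxon test for normal data

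| Assumed r | Variance ratio (1+r)/2 | Extra patients for the same precision, 2/(1+r) − 1 | Power, mean change | Power, rank test of change |
|---|---|---|---|---|
| 0.3 | 0.65 | 54% | 62% | 60% |
| 0.5 | 0.75 | 33% | 68% | 66% |
| 0.7 | 0.85 | 18% | 73% | 71% |
| 0.9 | 0.95 | 5% | 78% | 76% |

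A rank-based analysis that did adjust for baseline would have about Φ(2.802 × √(3/π) − 1.960) = 78% power on the same footing. Under these assumptions nearly all the loss comes from the change score and little from ranking.

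**The case against.** The strongest reply is that the sentence names no test. Rank ANCOVA, site-stratified rank tests, Hodges-Lehmann estimates and bootstrap intervals are all non-parametric, and a SAP is promised. That stands as far as it goes: the protocol does not say the analysis is unadjusted, nor that only a p-value will be reported. It does not undo the commitment to changes in score, which is in the text.

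It is also fair that (1+r)/2 compares two mean-based analyses under a linear relation and equal variances. For skewed or bounded scores a rank method can be more efficient than least squares, so the figures are indicative only. The loss is small if r is high.

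A reader might infer more than the documents support:

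- **That baseline information is discarded.** A change score uses the baseline. It uses it with a fixed coefficient of 1.
- **That the comparison is biased.** Under randomisation it is not. Chance baseline imbalance is part of the variance already counted.
- **That site cannot be handled.** Rank tests can be stratified by site.
- **That all secondary outcomes are affected.** InterRAI outcomes are left open, and length of stay, readmission and level of care are not score changes of this kind.
- **That the cost-utility analysis would lack a mean EQ-5D difference.** The Economic Analysis section describes a separate analysis, whose outcome data "will enable both cost-effectiveness and cost-utility analyses to be performed". Means can be computed from patient-level data whatever test is used elsewhere.
- **That day 14 should be the main time point.** The SPPB is taken "on the 14th day and at discharge or exit from the project, using the Short Physical Performance Battery", but EQ-5D and the exercise scales have no day-14 assessment, and a patient discharged earlier has none either.

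**Conclusion.** The point holds, limited to SPPB, EQ-5D and the other scale scores analysed as change from baseline. The protocol fixes a less precise analysis than its own data allow, and does so before the distributions are known. The variance of a baseline-adjusted comparison would be 0.65 to 0.85 of the change-score variance for assumed r of 0.3 to 0.7, and 0.95 at r = 0.9. This rests on equal variances, one follow-up per comparison, mean-based methods and correlations the protocol does not supply. The direction does not depend on equal variances for mean-based methods. For rank methods both direction and size are less certain. The sentence should be changed, but it is an improvement to secondary analyses: it exposes no wrong figure and does not touch the primary comparison.

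**What to change.** Replace the sentence on changes in scores with wording such as:

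> Follow-up SPPB, EQ-5D and exercise self-efficacy and outcome-expectation scores will be compared between arms by regression on arm, baseline value and site, with robust standard errors. Where a score is short or strongly skewed, proportional-odds regression or rank ANCOVA with the same covariates will be used. Results will be reported as an adjusted difference (or adjusted odds ratio from the proportional-odds model) with a 95% confidence interval. Rank tests of change from baseline are sensitivity analyses.

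The SAP should name the model for each score before outcome data by arm are seen. Rank ANCOVA supplies mainly a test, so an adjusted difference should be reported beside it. The InterRAI sentence can stay as it is.

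The cost is one sentence of protocol text, carried into the SAP, and a little more analysis work. No new data or patients are needed. The downside is some modelling assumptions for bounded scores, which the robust standard errors and the rank-based sensitivity analysis cover.

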## Economic Analysis

A "with-in trial" economic analysis will be undertaken from the perspective of the healthcare system. The research costs will be excluded from this analysis so that the intervention group (with daily feedback on walking times) can be compared to a usual care group (who receive general discussion around mobility goals). This enables results to be generalised beyond a research setting.

We will collect data to accurately record costs at the patient and ward levels. Cost data will include staff and technician time in applying the accelerometer, downloading and analysing data, and AM time to feedback the previous day's walking achievements to the patient. Ward costs include a national average per diem cost for length of stay and any costs for readmissions during the follow-up period. Equipment costs will include accelerometers, computation and printing. The outcome data (including walking time, length of stay and quality of life) will enable both cost-effectiveness and cost-utility analyses to be performed. Sensitivity analyses will enable these estimates to be adjusted for expected cost reductions associated with increased use (more patients per ward will secure economies of scale) and price reduction as the technology improves.

